Determine whether the use of a smart bassinet (SB) augments infant sleep and improves maternal sleep during the first 6 months post partum compared to the use of a traditional bassinet (TB). (1) Hypothesis 1a: Infants who sleep in SB will have better sleep (ie, diary and Brief Infant Sleep Questionnaire as maternally reported) [40] than those who sleep in TB. Outcomes will include maternally reported sleep duration, awakenings, as well as objectively assessed (actigraphy) wake after sleep onset and sleep onset latency. (2) Hypothesis 1b: Mothers of infants who sleep in SB will have better subjectively reported (ie, diary and Pittsburgh Sleep Quality Index) and objectively assessed (actigraphy) sleep compared to those of infants who sleep in TB. Outcomes will be the same as those for infants.Determine the effect of SB on maternal postpartum depressive and anxiety symptoms and evaluate the model that the association between SB and postpartum depressive symptoms is mediated by both infant and maternal sleep. (1) Hypothesis 2a: Mothers of infants who sleep in SB will have fewer postpartum depressive symptoms over time (ie, Edinburgh Postnatal Depression Scale) compared to those of infants who sleep in TB. (2) Hypothesis 2b: SB improves infant sleep, which then predicts better maternal sleep, and thereby predicts lower maternal depressive symptoms.Compare the trajectory of immune system function from late pregnancy through post partum between participants with and without PMADs and between SB and TB groups. (1) Hypothesis 3a: Peripheral cytokines, immune cells, and stimulated cytokine profiles of women with PMADs assessed in late pregnancy and at 3 and 6 months post partum will indicate greater innate immune activity compared to those of women without PMADs. (2) Hypothesis 3b: Mothers of infants who sleep in SB will exhibit lesser innate immune dysfunction than mothers of infants who sleep in TB.Exploratory aim: Evaluate whether the elevated risk demonstrated by previously identified PMAD epigenetic biomarkers at the TTC9B and HP1BP3 genes can be modified by using an SB. We hypothesize that the elevated risk will be reduced in the SB group compared to that in the TB group.

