#### Primary Maternal Assessments

The Consensus Sleep Diary [50] will collect subjective sleep, while actigraphy will be contemporaneously used to derive objective sleep data. The Pittsburgh Sleep Quality Index [51] will measure habitual sleep quality. The Edinburgh Postnatal Depression Scale [52,53] will be used to assess changes in the depressive symptoms over time. The Generalized Anxiety Disorder Scale-7 items [54] and the Perinatal Anxiety Screening Scale [55] will be used to assess anxiety symptoms over time.

Participants will have their blood drawn (up to 20 mL) at enrollment, 3 months post partum, and 6 months post partum at a Quest Diagnostics laboratory near them (Figure 1). Briefly, blood collection kits with ethylenediaminetetraacetic acid tubes will be mailed to participants with a requisition form and a laboratory directive (from Quest) that provides the Quest Diagnostics Patient Service Center instructions on how to collect and process the study kit. Blood samples will be shipped in a temperature-controlled fashion to the Psychoneuroimmunology in Pregnancy & Postpartum (PIPPI) laboratory at Weill Cornell Medical College for analysis. Measurements of circulating cytokines, stimulated cell assays, and flow cytometry analysis will be conducted to evaluate the role of immune dysregulation.

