#### Mean Differences

Initial analyses will be performed to verify that the random assignment procedure successfully equalized participants between the treatment and control groups on the preintervention variables. Thus, MANOVA will compare these 2 groups on the entire set of preintervention baseline measures. A chi-square test will verify that both groups have the same distribution of infant boys and girls. As participants will be randomized to groups using a random number generator, baseline equivalency of the 2 groups is anticipated.

Six separate mixed 2 (treatment vs control) × 6 (assessment period) MANOVA models will be conducted. Specifically, to assess hypothesis 1a (aim 1), the model (model 1) will be applied to the infant sleep quality outcome measures. To address hypothesis 1b (aim 1), the analysis (model 2) will be applied to maternal postpartum sleep quality outcome measures. To evaluate hypothesis 2a (aim 2), the model (model 3) will be applied to the maternal postpartum depression outcomes. To examine hypothesis 3a (aim 3), the model (model 4) will be estimated on the measures involving peripheral cytokines, immune cells, and stimulated cytokine profiles. To examine hypothesis 3b (aim 3), the model (model 5) will be undertaken on the measures of T-cell dysfunction. Furthermore, to examine the exploratory aim, the model (model 6) will be estimated on the epigenetic biomarkers.

In each of the mixed MANOVA models, several follow-up analyses will be conducted to examine the results. First, a mixed (between-subjects and within-subjects) analysis of variance will be applied on each specific outcome. Second, independent 2-sided *t* tests will assess mean differences between the treatment and control group (at each timepoint) on each outcome. Third, dependent 2-sided *t* tests will permit scrutiny of the temporal change in mean scores between every 2 timepoints on every outcome. Fourth, the longitudinal trajectories across the entire 6-month period for both the treatment and control groups will be graphed using 95% CIs to provide a visual tool to offer insights to understand the effectiveness of the RCT.

Prior to conducting analyses, the normal distribution of all the measures will be inspected. If a variable is evidenced to be nonnormally distributed, then the bootstrapping variant of these statistical techniques instead will be performed to obtain corrected *P* values [84].

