### Statistical Analyses for Immune Measurements

The initial statistical approach will include a descriptive cross-sectional analysis at each timepoint, both for quality assurance and to attain a better understanding of the distributions of the immune cell and cytokine profile variables for use in subsequent analyses, including the need for any transformations (ie, logarithmic transformation to symmetrize the residuals). Factor analysis will be employed as a means of data reduction to probe latent cytokine profiles reflected across the manifest indicators (eg, tumor necrosis factor-α, IL-6, IL-1β). We will first compare levels of a combined score of peripheral innate immune cytokines and frequency of maternal immune cells between women who do and do not develop PMADs in separate models to evaluate cross-sectional effects, employing a multivariable linear regression model to adjust for relevant covariates (eg, gestational age, BMI). Similar models will be repeated for maternal cytokines and innate cell recruiting factors as produced by the stimulated cells. Second, we will test whether the magnitude of group difference varies across the study period in a longitudinal analysis. We will fit a generalized linear population-average model estimated using generalized estimating equations with exchangeable working correlation structure to account for within-women correlation of mood measures. The model will include the relevant immune markers identified in the cross-sectional analyses, indicators for visit and group, as well as any relevant interaction terms (immune marker by group or immune marker by visit). The models will adjust for baseline severity of depressive symptoms and psychotropic medication use. Standard model checking will be performed, and the most parsimonious model will be selected based on the Akaike information criterion or quasi-likelihood information criterion for generalized estimating equations models. To test the within-group effects of severity of PMAD symptoms, the dichotomous group variable will be replaced by continuous Edinburgh Postpartum Depression Scale and Generalized Anxiety Disorder Scale-7 item scores in analytic models and restricted to only the subset of women with significant PMAD symptoms.

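### Models 4 and 5 do not match hypotheses 3a and 3b, cannot be fitted over six periods when immune blood is drawn three times, and the immune GEE leaves its response unclear

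*Protocol article*

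**What the plan says.** The aims in the Introduction set two immune hypotheses.

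- **Hypothesis 3a** compares women with and without PMADs. It expects that the immune measures of affected women "will indicate greater innate immune activity compared to those of women without PMADs", and it names late pregnancy and 3 and 6 months post partum as the assessment times.
- **Hypothesis 3b** compares the arms: "Mothers of infants who sleep in SB will exhibit lesser innate immune dysfunction than mothers of infants who sleep in TB".

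The Mean Differences section states the analysis: "Six separate mixed 2 (treatment vs control) × 6 (assessment period) MANOVA models will be conducted". Model 4 is assigned to 3a and covers circulating cytokines, immune cells and stimulated cytokines. For 3b it says: "To examine hypothesis 3b (aim 3), the model (model 5) will be undertaken on the measures of T-cell dysfunction".

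Primary Maternal Assessments fixes the sampling: "Participants will have their blood drawn (up to 20 mL) at enrollment, 3 months post partum, and 6 months post partum". Table 1 and the Ethics Approval section give the same three times.

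Statistical Analyses for Immune Measurements adds a second route. Its first step is a multivariable linear regression that compares immune measures between women who do and do not develop PMADs. Its second step is a GEE whose working correlation is there "to account for within-women correlation of mood measures". The GEE's predictors are the immune markers, visit and group. To study severity, "the dichotomous group variable will be replaced by continuous Edinburgh Postpartum Depression Scale and Generalized Anxiety Disorder Scale-7 item scores".

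**The concern.** The article maps each hypothesis to a model, so the mapping can be checked directly. In aim 3 it does not hold. An analyst who follows the text would report an arm effect as the answer to a question about PMAD status, and a T-cell result as the answer to a question about innate immunity. The six-period layout would also call for immune values that nobody collects. The longitudinal immune model cannot repair this as it stands, because its response is not named and its terms conflict.

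If this stays open, someone must choose the contrast, outcome and visits for aim 3 later, possibly with the data in view. The abstract lists lower immune dysregulation with SB among the hypotheses to be tested, and 3b is the only immune hypothesis that rests on the randomisation.

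**Working it through.** This is a question of specification, so most of the check sets the sections side by side.

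**1. Factor, visits and outcome**

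| | Hypothesis (Introduction) | Model (Mean Differences) | Match? |
|---|---|---|---|
| 3a / model 4: factor | PMAD vs no PMAD | treatment vs control | no |
| 3a / model 4: visits | late pregnancy, M3, M6 | 6 periods | no |
| 3a / model 4: outcome | cytokines, immune cells, stimulated cytokines | the same | yes |
| 3b / model 5: factor | SB vs TB | treatment vs control | yes |
| 3b / model 5: visits | three draws | 6 periods | no |
| 3b / model 5: outcome | innate dysfunction | T-cell dysfunction | no |

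Each model has two of the three faults. T cells belong to adaptive immunity. Innate measures are available: the Flow Cytometry Analysis section gates monocytes and natural killer cells, and the Cytokine Analysis section uses a proinflammatory panel.

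**2. Visit count**

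- Study timepoints (Study Design): late pregnancy plus M1 to M6, which is 7. Six assessment periods most naturally means M1 to M6.
- Immune draws: 3 (late pregnancy, M3, M6), of which 2 fall within M1 to M6.
- Periods without immune data: 6 − 2 = 4 (M1, M2, M4, M5).
- Cells in the layout: 2 × 6 = 12. Cells that can hold immune data: 2 × 2 = 4.
- If the six periods were instead meant to include late pregnancy, at most 3 of the 6 would hold immune data.

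No participant can supply six periods. Imputation or full-information likelihood does not help, because the missing values are unobserved for everyone.

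**3. What model 4 says about 3a**

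An illustration with assumed inputs: 171 women per arm (342/2), PMAD rates of 12.2% and 26% (the abstract's figures for spouses and service women), an assumed difference of 0.5 SD in the immune measure by PMAD status, no arm effect, two-sided 5% level, 4,000 simulations each.

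| PMAD rate | Arm contrast rejects | PMAD contrast rejects |
|---|---|---|
| 12.2% | 4.4% | 84% |
| 26% | 5.6% | 98% |

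The arm contrast rejects at about the nominal level, so it carries no information on 3a even when the PMAD difference is real. The 0.5 SD is not from the documents, which give no immune effect size.

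**4. The GEE**

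- If the response is mood, as the phrase on correlation implies, then PMAD group, and later the EPDS and GAD-7 scores, are mood predictors of mood.
- If the response is an immune marker, as the preceding comparison of immune levels suggests, then immune markers are also listed among the predictors.

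Either way the model needs restating. Nothing in that section compares SB with TB.

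**The case against.** The strongest reply is that both contrasts do appear in the document. The cross-sectional regression compares innate cytokine scores and immune cells between women with and without PMADs, which is the contrast of 3a on an immune outcome. Model 4, taken literally, compares the arms on measures that include innate ones, and the follow-up t tests would compare the arms at M3 and M6. On this view the fault is labelling plus a layout copied from the monthly questionnaires.

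Much of this stands. A reader might infer that aim 3 has no valid test at all. The documents do not support that: 3a has its cross-sectional regression, and an arm comparison on innate measures exists within model 4. What remains is that this arm comparison is assigned to the wrong hypothesis, that model 4 cannot be fitted over six periods, and that the longitudinal part of 3a depends on an unclear GEE.

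Three other strong readings also fail.

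- **The GEE group effect is significant by construction.** This needs mood to be the response, which is inferred from one phrase and never stated. The phrase may be a drafting slip.
- **Study arm confounds the PMAD–immune association.** 3a is a question of association. With the plan's d = 0.33 for depression, r = 0.33/√(0.33² + 4) ≈ 0.16. If the arm effect on immune markers were equally large, the induced correlation would be about 0.16 × 0.16 ≈ 0.03.
- **Only about 234 women would be analysed** (342 × 0.85 × 0.93³). This assumes independent missed draws and complete-case analysis, while the Missing Data section plans full-information likelihood or multiple imputation. The Power section also targets 393 women, not 342.

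**Conclusion.** The point holds as a mismatch between hypotheses, models and sampling. Model 4 has the wrong factor and visit count for 3a. Model 5 has the wrong outcome and visit count for 3b. Four of the six postpartum periods have no immune data, so neither model can be run as written. The GEE has conflicting terms on either reading of its response. These conclusions rest on the text and a count of draws; only the simulation uses outside assumptions, and nothing depends on it.

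This should be fixed. It is not fatal: the cross-sectional test of 3a is sound in form, the data needed for 3b are collected, and the sleep and mood analyses are untouched.

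**What to change.** - **Hypothesis 3a:** state a repeated-measures model with the immune measure as outcome, and PMAD status, visit (late pregnancy, M3, M6) and their interaction as predictors.
- **Hypothesis 3b:** state an SB versus TB model on the innate markers using the same three draws, for example M3 and M6 as outcomes with the late-pregnancy value as covariate. Report T-cell measures separately.
- **Layout:** exempt the immune models from the six-period design.
- **GEE:** restate it with the immune marker as the response, and remove immune markers from its predictors.

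The cost is a rewrite of the model-assignment paragraph and the GEE text. No new data, assays or participants are needed. The article expects analysis to be complete by July 2028, and the change should be dated before any immune results are seen by arm or PMAD status.

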**Maternal assessments (primary)**														
	Sleep diary			✓		✓		✓		✓		✓		✓
	Actigraphy			✓		✓		✓		✓		✓		✓
	Pittsburgh Sleep Quality Index	✓		✓		✓		✓		✓		✓		✓
	Edinburgh Postnatal Depression Scale	✓		✓		✓		✓		✓		✓		✓
	Generalized Anxiety Scale	✓		✓		✓		✓		✓		✓		✓
	Tasso blood collection kit (Epigenetics)	✓												
	Blood samples (inflammation)	✓						✓						✓

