### Epigenetic Biomarker Testing

#### Blood Draw Collection

Upon enrollment, participants will be sent supplies from TruDiagnostic for blood collection, including a Tasso blood collection kit and a prepaid mailing kit to TruDiagnostic. Blood samples will be processed using the Illumina Human MethylEPIC beadchip. Methylation data for the *TTC9B*, *HP1BP3*, and *MS4A7* genes will be sent to [name] who will use the published algorithm for predicting postpartum depression risk to determine if the participant’s epigenetic methylation patterns are consistent with increased risk for postpartum depression. Participants will not be informed of their biomarker status, as we are still determining the clinical value of the biomarkers.

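### Model 6 makes a biomarker sampled once, before delivery, the outcome of a six-period repeated-measures model, so it cannot be fitted and does not address the exploratory aim

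*Protocol article*

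**What the plan says.** The Mean Differences section of the protocol article fixes a common form for the main analyses: "Six separate mixed 2 (treatment vs control) × 6 (assessment period) MANOVA models will be conducted". It then assigns one model to each hypothesis. The last assignment is "to examine the exploratory aim, the model (model 6) will be estimated on the epigenetic biomarkers". The same phrase introduces the dependent variables of the immune model: "the model (model 4) will be estimated on the measures involving peripheral cytokines, immune cells, and stimulated cytokine profiles".

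Table 1, under the primary maternal assessments, has a row for the "Tasso blood collection kit (Epigenetics" sample with a single tick, in the baseline column. The section on the epigenetic blood draw agrees: "Upon enrollment, participants will be sent supplies from TruDiagnostic for blood collection, including a Tasso blood collection kit". It says the methylation data are used "to determine if the participant’s epigenetic methylation patterns are consistent with increased risk for postpartum depression".

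The Introduction frames the exploratory aim as a change in biomarker-related risk: "We hypothesize that the elevated risk will be reduced in the SB group compared to that in the TB group".

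**The concern.** A mixed MANOVA with six assessment periods needs its outcome measured repeatedly. Methylation is measured once, and before the intervention can act. The model and the sampling schedule therefore contradict each other.

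The stated model also addresses a different question from the aim. The aim concerns effect modification: whether women whose methylation marks them as high risk have less excess depression with SB than with the traditional bassinet (TB). The outcome should then be mood, with the biomarker as a baseline modifier. Model 6 makes the biomarker the outcome. At stake is whether the exploratory aim has any usable prespecified analysis. If it has none, the replacement would be chosen after the data are in.

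**Working it through.** **1. Is methylation the outcome of model 6?** The section names only two factors, arm (2 levels) and assessment period (6 levels). Model 4 is described in the same terms, and there the phrase plainly names the dependent variables. Read consistently, the biomarkers are the dependent variables of model 6, and no biomarker factor is included.

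**2. Occasions required against occasions scheduled.**

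| Item | Count | Source |
|---|---|---|
| Assessment periods in model 6 | 6 | Mean Differences |
| Scheduled methylation samples | 1 (baseline) | Table 1; epigenetic blood draw section |
| Methylation samples in months 1 to 6 | 0 | Table 1 |
| EPDS assessments | 7 (baseline and months 1 to 6) | Table 1 |

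The next row of Table 1, blood for inflammation, has ticks at baseline, month 3 and month 6. The single epigenetic tick is therefore unlikely to be a table-extraction fault, and the text confirms it.

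**3. What can be estimated?** A 2 × 6 design has 12 cell means. If the six periods are months 1 to 6, no cell has methylation data. If the baseline value is allowed to stand as one of the six, 2 of the 12 cell means are estimable, one per arm. There is then no period effect and no arm-by-period interaction. If the baseline value is copied into all six periods, every within-woman difference is zero. The within-subject difference matrix then has rank 0, and the within-subject test is undefined. The listed follow-ups (tests at each timepoint, paired tests between timepoints, six-month trajectories) fail for the same reason.

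**4. What remains?** Only a comparison of baseline methylation between arms. Its expected difference under randomisation is zero. The same section already plans a MANOVA of all preintervention measures to check balance, so this comparison would add nothing.

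**5. Could that comparison reflect effect modification?** As an illustration, 2,000 simulated trials were run with N=342, 1:1 allocation, a standardised biomarker, a slope of 0.6 on a depression score in the TB arm, and residual SD 1 (slope and SD are assumptions).

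| Fall in slope under SB | Baseline methylation by arm: rejections | Arm × biomarker on depression: rejections |
|---|---|---|
| 0 | 5.0% | 5.0% |
| 0.3 | 4.9% | 79% |
| 0.6 | 5.4% | 100% |

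The arm comparison stays at chance level however strong the true modification is. The interaction model responds to it.

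**6. Does another stated model cover the aim?** Model 3 has depression as outcome but no biomarker term. The mediation model runs from arm through infant and maternal sleep to depression. The covariate list does not include the biomarker. The interaction terms in the immune analysis involve immune markers. None supplies an arm-by-biomarker term on mood.

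**7. What could a replacement detect?** This is context only and does not affect the finding. For the six-month mean, the smallest detectable interaction (two-sided 5%, 80% power), in SDs of a single monthly score, is

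[2 × (1.96 + 0.84) / √N] × [1 / √(p(1−p))] × √((1 + 5ρ)/6)

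where p is the proportion biomarker-positive and ρ the within-woman correlation. The documents give neither, so ρ = 0.4 to 0.7 and p = 0.50 to 0.15 are assumed. N is 342 × 0.85 ≈ 291 or 393 × 0.85 ≈ 334, because the article gives both totals.

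| p | N=291 | N=334 |
|---|---|---|
| 0.50 | 0.47 to 0.57 | 0.43 to 0.53 |
| 0.25 | 0.54 to 0.66 | 0.50 to 0.61 |
| 0.15 | 0.65 to 0.80 | 0.61 to 0.74 |

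Baseline EPDS adjustment would lower these values.

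**The case against.** The best defence is that the 2 × 6 label is shorthand. It is also attached to the immune models, although inflammation blood is drawn at only three visits. The article later gives those markers a different, workable analysis. The abstract, too, mentions the epigenetic question separately, after the sleep, mood and immune hypotheses. The authors may have meant biomarker status as a grouping factor with mood as the outcome. That is plausible, but the article does not say it: model 6 is assigned to this aim by name, and no alternative like the immune one is given. A separate analysis plan might repair this, yet the article itself states a model that its own schedule contradicts.

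A second objection concerns weight. The aim is exploratory, participants are not told their biomarker status, and no primary outcome, sample size or safety element depends on model 6. This objection stands and limits the severity.

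Two stronger readings are tempting. A reader might infer a 5% chance of falsely claiming that SB altered epigenetic risk. A model that cannot be fitted gives no P value. That figure would require analysts to fall back on the baseline comparison and then present it as a treatment effect, and the article states neither step. A reader might also infer that the interaction could be detected only at 0.66 to 0.92 SD. Those values belong to a single-timepoint contrast with 291 women, not to a model using six monthly scores.

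**Conclusion.** The point holds as a structural error. Model 6 calls for six occasions of a variable scheduled once, with none in the postpartum months, so it cannot be fitted. Its only reducible form repeats a balance check and is uninformative about the aim, and no other stated model fills the gap.

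This rests on reading the biomarkers as the dependent variables, which the parallel wording for model 4 supports, and on the single baseline sample that Table 1 and the text agree on. It does not depend on any sample-size or effect-size assumption. Because the aim is exploratory and the repair is simple, this should be fixed but does not threaten the trial's main conclusions.

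**What to change.** Replace model 6 with a repeated-measures model of EPDS over months 1 to 6. Its terms are arm, baseline biomarker risk status from the published algorithm, arm × biomarker, month and baseline EPDS. Report the arm × biomarker interaction with a 95% CI, and the arm effect within each biomarker group, labelled exploratory. Remove the 2 × 6 description and its follow-up tests for the biomarkers. If a detectable difference is quoted, compute it for this six-month model, with the sample size, biomarker prevalence and within-woman correlation stated as assumptions.

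The cost is about one sentence in the plan. Baseline methylation and EPDS at baseline and months 1 to 6 are already scheduled, so no visit, sample or questionnaire is added. The change should be dated before any analysis of outcomes by arm.

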**Methods:**

This study is a 6-month, parallel-arm, randomized controlled trial. Pregnant women (N=342) in the third trimester will be randomized at 1:1 ratio to use a smart bassinet (SB) or a standard commercially available bassinet (HALO BassiNest Swivel Sleeper 3.0; traditional bassinet [TB]) for up to 6 months after delivery. Participants will have their infants sleep in the bassinet, complete monthly web-based questionnaires, and record sleep data with diary and actigraphy for both the participants and their infants for 1 week each postpartum month. Blood samples will also be collected at baseline (late pregnancy) and at 3 months and 6 months post partum to assess immune functioning. The primary outcomes for this study will be postpartum mood (depressive and anxiety symptoms) and infant and maternal sleep. In addition, we are evaluating whether SB has a significant impact on immune functioning—a marker that physiologically connects sleep and mood symptoms.

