### Statistical Analysis

#### Power

Power analyses were performed using *P*<.05 (2-tailed) at .80 power, based on recommended guidelines [78-80]. The power analyses were conducted for each statistical technique to be pursued in aims 1 to 3: mixed (between-subjects and within-subjects) multivariate analysis of variance (MANOVA), mixed (between-subjects and within-subjects) analysis of variance, independent 2-sided *t* test, dependent 2-sided *t* test, correlation, and the mediational models involving structural equation modeling (based on the β coefficient). The pilot study collected similar measures from pregnant/postpartum women with a history of major depressive disorder who used SB or HALO TB. Hence, the power analyses were based on pilot sleep and mood data. Calculations revealed an average effect size across all postpartum timepoints (T1 to T6) between the treatment and control groups on the following measures: infant sleep (*d*=0.39), postpartum sleep quality (*d*=0.27), and postpartum depression (*d*=0.33). Based on these effect sizes, a sample size of 208 participants is needed for infant sleep, 434 participants for postpartum sleep quality, and 286 participants for postpartum depression to attain statistical significance. Thus, a final sample size of 393 participants will be targeted (allowing for an attrition rate of 15%).

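### Anxiety is a primary outcome with no treatment-versus-control comparison, and the three modelled primary constructs have no named contrast or stated gating for their monthly t tests

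*Protocol article*

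**What the plan says.** **Primary outcomes.** The Abstract (Methods) states: "The primary outcomes for this study will be postpartum mood (depressive and anxiety symptoms) and infant and maternal sleep". Aim 2 in the Introduction includes the effect of SB on anxiety as well as depression. Table 1 lists the generalized anxiety scale among the primary maternal assessments, at baseline and in all six postpartum months. The section Primary Maternal Assessments names both the GAD-7 and the Perinatal Anxiety Screening Scale. The Abstract (Results) says the models will test whether SB reduces mood symptoms more than TB does.

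**Models.** Hypothesis 2a names the Edinburgh scale (EPDS) only. The section Mean Differences assigns all six MANOVA models to a hypothesis or aim; for hypothesis 2a, "the model (model 3) will be applied to the maternal postpartum depression outcomes".

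**Follow-up tests.** Each MANOVA is followed by a mixed ANOVA per outcome, by independent t tests of "mean differences between the treatment and control group (at each timepoint) on each outcome", and by dependent t tests that "permit scrutiny of the temporal change in mean scores between every 2 timepoints on every outcome". None of these steps is made conditional on an earlier one. No primary month, primary measure or averaged contrast is named. The only correction of P values mentioned there is a bootstrap for non-normal data.

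**Power.** Sizes are given for three constructs: "a sample size of 208 participants is needed for infant sleep, 434 participants for postpartum sleep quality, and 286 participants for postpartum depression". Anxiety has neither an effect size nor a sample size.

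**The concern.** There are two linked problems.

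First, the outcome list and the analysis plan disagree. Mean Differences allocates every model by number, so anxiety has not simply been left for later. Followed literally, the plan yields no SB-TB result for one of its primary outcomes.

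Second, the constructs that are modelled have no single quantity on which a claim would rest. The article sets out many between-arm comparisons (by outcome and by month) without saying which is confirmatory. The study is unblinded and many outcomes are self-reported, so a favourable month or measure could be emphasised after the fact, and nothing in the text would mark it as one of many.

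**Working it through.** **1. Where anxiety appears**

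| Place | Anxiety included? |
|---|---|
| Abstract, primary outcomes | Yes |
| Aim 2 | Yes |
| Table 1 and Primary Maternal Assessments | Yes, as primary |
| Hypothesis 2a | No (EPDS only) |
| Models 1-6, Mean Differences | No (model 3 is depression) |
| Power | No |
| Statistical Analyses for Immune Measurements | GAD-7 only, as a severity variable in women with significant symptoms |

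The last row relates immune markers to symptom severity. It does not compare bassinets.

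**2. What the stated sample sizes imply**

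The inputs are d = 0.39, 0.27 and 0.33, two-sided .05, 80% power and 1:1 allocation (Power section). The formula is n per arm = 2(1.960 + 0.842)²/d².

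- Infant sleep: 103.2, rounded up to 104, total 208 (stated 208).
- Maternal sleep quality: 215.3, rounded up to 216, total 432 (stated 434).
- Depression: 144.1, rounded up to 145, total 290 (stated 286).

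All three agree with the stated figures within 3%. Each construct was therefore sized as one unadjusted two-group comparison using the whole .05.

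**3. Number of between-arm tests**

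The number of measures is an assumption, because the article does not fix a list. Hypotheses 1a and 1b suggest four infant sleep measures (duration, awakenings, wake after sleep onset, sleep onset latency) and five maternal ones (the same four plus the Pittsburgh index). With EPDS that makes 10.

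- Between-arm monthly t tests: 10 × 6 = 60. Expected false positives with no effect: 60 × .05 = 3.0.
- Month pairs for the dependent t tests: 6 × 5/2 = 15 per measure.

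The two anxiety scales are left out of the count because no model tests them.

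**4. Chance of at least one P<.05 with no effect**

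This comes from a simulation of multivariate normal test statistics, counting |z| > 1.96. The correlations are assumed: .5 to .7 between months and .3 to .5 between outcomes. The t tests are treated as ungated, each at .05.

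| Set of tests | At least one, either direction |
|---|---|
| Three single tests, one per modelled construct | 12%-14% |
| One measure, six months | 16%-21% |
| One measure per construct, 18 tests | 37%-49% |
| Ten measures, 60 tests | 69%-86% |

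For the 60 tests, the chance of at least one result favouring SB is about 37%-53%. If the tests were independent, the first row would be 1 − .95³ = 14.3% and the third 1 − .95¹⁸ = 60.3%. With a different correlation pattern (the same correlation between constructs whatever the month), the 18 tests give about 35%-47%, so the result does not hinge on the pattern chosen.

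**The case against.** The best defence has four parts.

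- **Scope.** This is a condensed article, and alpha allocation and test order are commonly left to an analysis plan that is not shown. That is a fair limit on the multiplicity part. It does not cover anxiety, where the published outcome list and the published model allocation disagree.
- **Structure.** Each hypothesis has one MANOVA, and the t tests are described as follow-ups. If the MANOVA gated them, the relevant figure would be close to the 12%-14% for three tests. That is correct, but the text states no gating and names no contrast.
- **Anxiety might be implied.** The Abstract (Results) speaks of mood symptoms, and model 3 refers to outcomes in the plural. However, hypothesis 2a, which model 3 is there to test, names EPDS alone, and no anxiety effect size is given.
- **Paired tests.** They are offered only to examine change over time.

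Several stronger readings are tempting and are not supported:

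- A reader might infer that some month will almost surely favour SB by chance. The 69%-86% counts both directions; for SB alone it is about 37%-53%.
- A reader might infer that every follow-up test is declared at .05. That level is stated only for the power analyses; its use here is an inference.
- A reader might infer that anxiety enters no model at all. GAD-7 does enter the immune models.
- A reader might infer that N = 342 was sized for EPDS, or that paired changes are presented as evidence of efficacy. The article says neither.

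**Conclusion.** The point holds in this form. The anxiety inconsistency is the firmest part: it rests on the article's own text and needs no assumption. A primary outcome has no between-arm comparison and no power statement.

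The second part also holds, with less certainty because an unseen analysis plan may address it. Three constructs are each sized at the full .05 and followed by ungated monthly comparisons with no primary contrast. The error rate runs from about 12%-14% if each construct has a single test to 69%-86% if all 60 monthly t tests on ten measures are read equally. Those figures depend on the assumed correlations, the assumed count of measures, a .05 level for each test and no gating. This is a defect in how results could be claimed, not in the design or data collection, and it should be settled before outcomes are compared by arm.

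**What to change.** 1. **Anxiety.** Add the GAD-7 and the Perinatal Anxiety Screening Scale to hypothesis 2a and to the mood treatment comparison, and name one of them as the primary anxiety measure. Otherwise, stop calling anxiety primary throughout. If both stay, confirm the schedule of the Perinatal Anxiety Screening Scale, which has no row of its own in Table 1.
2. **Contrast.** Name one measure and one SB-TB contrast for each primary construct, for example the difference averaged over months 1-6.
3. **Error control.** Prespecify an order of testing or an alpha allocation across those contrasts. The choice is the sponsor's.
4. **Monthly results.** Report them as estimated differences with confidence intervals.
5. **Paired tests.** State that month-to-month changes are descriptive and are not evidence of efficacy, since infant sleep and maternal mood can change with time in both arms.

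The cost is wording, with no change to visits or instruments. With a fixed order, a miss early on makes later outcomes descriptive. Splitting alpha costs sample size: as an illustration, .05/4 would raise the evaluable totals to 294 (infant sleep), 612 (maternal sleep) and 410 (depression). Anxiety cannot be sized until an effect size is given.
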